### Clinical assessment

Subjects will be assessed by independent clinicians who will not be involved in the direct clinical care of any of them. They will be psychiatrists, MA-level chartered psychologists or PhD-level chartered psychotherapists. A semistructured interview will be used with the aim of identifying relevant DSM-IV diagnostic criteria for GAD in the subjects.

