### Psychometric assessment

The following psychometric questionnaires will be administered to each patient at pre-treatment, upon completion of the clinical trial, and after 6-month and 12-month follow-up periods:

- PSWQ – Penn State Worry Questionnaire – [18]. The PSWQ is the only existing questionnaire specific for GAD with an extensive validation on Italian population. It analyzes symptoms of pathological worries that characterize this disorder.

- BAI – Beck Anxiety Inventory – [19]. The BAI is a standardised and well-used assessment measure with good psychometric properties used to assess anxiety. It is a 21-item scale which covers cognitive, behavioural and physiological symptoms of anxiety.

- Anti – Anxious Thoughts Inventory – [20]. The AnTI included 22 items that investigate 3 different categories of worries: social worries, worries linked to health and the metacognitions about worry (fear of fear). The available data show that the AnTI questionnaire is sensitive to treatment effects.

- CID – Anxiety and Depression Scales of the Clinical Interview for Depression – [21]. The CID anxiety scale consists of 4 items rated on a 7-point scale. The CID depression scale includes 10 items.

- STAI – State-Trait Anxiety Inventory – [22]. The STAI measures a person's situational (or state) anxiety, as well as the amount of anxiety a person generally feels most of the time (trait). The two scales contain 20 items each, which may be scored 1 (not at all) to 4 (very much so).

Immediately before and after each treatment session subjects will be also asked to rate their levels of subjective anxiety on the Visual Anxiety Scale (VAS-A). In order to verify if there is a positive correlation between the treatment efficacy and the sense of presence experienced by the patients during the treatment sessions, the Itc-Sense of Presence Inventory (ITC-SOPI) [23] will be administered to each patient exposed to the VR environment after each session. The ITC-SOPI is a questionnaire composed by 44 items, that investigates the sense of presence experienced during the VR exposure.

Moreover, as homework, patients will be asked to fill some forms regarding their relaxing experiences.

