### Experimental design

Patients included in the study will be randomly assigned to one of the following three conditions:

(I) VR: subjects will be taught to relax using VR relaxing environments and audio-visual mobile narratives;

(II) non-VR: patients will be taught to relax using the same relaxing narratives proposed to the VR group, but without the VR support;

(III) WL: patients included in the waiting list group will not receive any kind of relaxation training.

Psychometric and psychophysiological outcomes will serve as quantitative dependent variables, while subjective reports of participants will be used as qualitative dependent variables.

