### Clinical protocol

The clinical protocol will be based on 7 weeks of Applied Relaxation (AR) training (2 sessions per week). Patients will be taught coping skills which enable them to relax rapidly, in order to counteract and possibly eliminate the anxiety reactions.

We will now describe the protocol in details, following the one developed by Ost in 1987 [26]. The sessions will be the same for both groups (VR and non-VR), with the only difference that the VR group is presented with audio narratives accompanied by virtual relaxing environments, while the non-VR group only hear the narratives.

The protocol will follow the following schema:

- Session one: the therapist clearly explains the patient the role of bodily arousal in the maintenance of anxiety and underlines the fact that relaxation procedures can be useful to reduce the autonomic arousal. A general description of the method used in the following sessions will be given to the patient. After an oral presentation, patients will receive a short written description of the rationale. In this way, they will have the possibility to read the text as many times as they want, to ask questions about unclear points and to study it at home.

The following is an example of the text given to the patients (adapted from Ost, 1987):

"When a person suffers from an excessive anxiety usually manifests three different components in his/her reaction: physiological (increased heart rate, blood pressure, sweating etc.), behavioral (trying to escape from the anxious situation, trembling etc.), and subjective (negative thoughts like 'I am going to faint or lose control' etc.). The strength of these components varies between patients, but previous research has found that most people experience some physiological changes, followed by a negative thought, which increases the physiological reaction, generating a vicious circle.

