One good way of breaking this development is to focus on the physiological reactions and learn not to react so strongly. The method we are going to use to achieve this is called applied relaxation. The aim of this technique is to learn a skill of relaxation, which can be applied very rapidly and in any real-life situation. This skill can be compared to any other skill, e.g. learning to swim, ride a bike, or drive a car, in that it takes time and practice to be learned, but once you have mastered it, you can use it anywhere. You are not restricted to the calm and non-stressful situation in the therapist office or your own home.

The goal of the treatment is to be able to relax in few sessions and to use this skill to counteract, and eventually get rid of, the physiological reactions you usually experience in anxious situations. To achieve this we are going through a gradual process starting with tensing and relaxing different muscle groups.

The next step teaches you to connect the self-instruction 'Relax' to the bodily state of relaxation. After that it is time for the rapid relaxation, which you practice many times a day in non-stressful situations. Finally, you reach the stage of applying the skill in anxious situations, and I will take you to different anxiety-arousing situations coaching you how to apply the relaxation at the first signs of anxiety in these situations. Applied relaxation is thus a skill that most people can acquire with the right instructions and practice. It is a 'portable' skill that can be used in almost any situation, e.g. when having problems in falling asleep.

During the entire protocol you'll be guided by relaxing narratives (and images) that suggest you how to reach a relaxed state".

The second part of the session one will be dedicated to fill the following questionnaires: PSWQ, BAI, AnTi, CID and STAI.

The following sessions will be dedicated to teach patients to recognize early signals of nervousness and to cope with anxiety. Each session lasts about one hour and is divided in four parts: homework checking, relaxation, comments about the experience (debriefing) and new homework assignments. Immediately before and after the relaxation phase physiological and psychometric measures will be taken in order to measure the objective and subjective effects of relaxation on the patient. The relaxation setting consists in a very quite room scarcely enlighten in which the patient sits in a comfortable armchair.

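### The only first administration of the five questionnaires that the article describes comes after the treatment rationale in session one, which the waiting-list arm does not have

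*Protocol article*

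**What the plan says.** All references are to the protocol article.

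- **Psychometric assessment:** PSWQ, BAI, AnTI, CID and STAI are to be "administered to each patient at pre-treatment, upon completion of the clinical trial, and after 6-month and 12-month follow-up periods".
- **Clinical protocol, session one, opening:** the therapist explains the part that bodily arousal plays in anxiety and "underlines the fact that relaxation procedures can be useful to reduce the autonomic arousal". Next comes the paper version: "After an oral presentation, patients will receive a short written description of the rationale".
- **Clinical protocol, session one, later:** "The second part of the session one will be dedicated to fill the following questionnaires: PSWQ, BAI, AnTi, CID and STAI".
- **Clinical protocol, who attends:** "The sessions will be the same for both groups (VR and non-VR"). The waiting list is not mentioned there.
- **Experimental design:** included patients are randomised to three conditions, and "patients included in the waiting list group will not receive any kind of relaxation training".
- **Trial analysis:** each patient's change in the psychometric measures is calculated and tested by paired t-tests in intervention and control groups. Analysis of variance is used for baseline characteristics and for overall improvement.

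**The concern.** A baseline for a three-arm comparison should be taken under the same conditions in every arm, before anything that differs between arms can affect it. As described, treated patients complete theirs in a therapy session, just after hearing and reading why the treatment should help, and very probably knowing that they are not on the waiting list. Waiting-list patients have no such session.

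Self-reported anxiety can plausibly respond to reassurance, expectation or knowledge of the assigned arm. If it does, the starting value of the treated arms moves and that of the waiting list does not, or moves differently. Because the analysis is built on change, the displaced starting value becomes part of the result. It cannot be recovered once patients are enrolled.

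**Working it through.** The article gives no figure on this point, so there is nothing to reproduce. The check is a comparison of sections, followed by an illustration on stated assumptions.

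**Step 1. Is the session-one administration the baseline?** The sentence does not call it that. But the five instruments are the same five that Psychometric assessment lists for pre-treatment, and no other first administration is described. This is an inference, and a natural one.

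**Step 2. What precedes it?** In the order given, the oral rationale, then the written rationale, then the questionnaires. No relaxation exercise is described in session one; muscle relaxation starts in sessions 2–5.

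**Step 3. Does it follow allocation?** No sentence gives the order of randomisation and first questionnaire. However, patients are randomised on inclusion, the sessions are described for the two treated arms only, and the example patient text has a bracketed mention of images that looks specific to the VR arm. A patient sitting in session one has therefore been assigned to a treated arm. This is a strong inference, not a stated fact.

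**Step 4. Can the waiting list be measured under the same conditions?** No. It has no session one, so its baseline cannot follow the rationale in a therapy session.

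**Step 5. How does a shift reach the result?** Let the baseline of the treated arms be moved by s, and that of the waiting list not at all. With change = final − baseline:

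- treated minus waiting list: bias = −s, so the whole shift passes into the contrast;
- VR minus non-VR: bias = −(s_VR − s_nonVR), which is 0 if the shift is equal in the two arms.

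**Step 6. Illustration.** Inputs: 25 per arm (Subjects section). Assumed, not in the article: SD of change = 1, two-sided test at 0.05, normal approximation, no true effect, and the values of s, in units of the SD of change.

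Standard error of the difference = √(2/25) = 0.283.

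False-positive rate = Φ(s/0.283 − 1.96) + Φ(−s/0.283 − 1.96).

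For s = 0.2: 0.2/0.283 = 0.707, so Φ(−1.253) + Φ(−2.667) = 0.105 + 0.004 = 0.109.

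| Assumed shift s (SD) | False-positive rate against waiting list |
|---|---|
| 0 | 5.0% |
| 0.1 | 6.4% |
| 0.2 | 10.9% |
| 0.3 | 18.6% |
| 0.5 | 42.4% |

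The rate is the same for either sign of s. The sign matters when there is a true effect. If the rationale lowers reported anxiety at baseline, the benefit against the waiting list is understated; if session one raises it, the benefit is overstated.

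**The case against.** The strongest case on the other side has four parts.

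**The main comparison may be untouched.** The first hypothesis in Aim of the study compares VR with traditional relaxation. Both arms have the same session one at the same time, so a common shift cancels. This stands. A reader might infer that the VR versus non-VR result is biased, but the article does not support that: the only arm-dependent element visible in session one is the bracket about images. The threat is to comparisons with the waiting list.

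**The questionnaires do precede relaxation training.** This also stands. A reader might infer that baseline is taken after relaxation practice has begun, but none is described before session two. What comes first is the rationale and, probably, knowledge of the arm. That is a milder exposure, but it still falls on the treated arms alone.

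**A condensed article need not say when the waiting list is assessed.** True, and that silence is not the point here. Nor does the article leave the waiting list without a baseline: the questionnaires "will be administered to each patient at pre-treatment". The point rests on what is stated, namely the place of the questionnaires in session one and the absence of that session in the third arm.

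**Independent assessors are promised.** A reader might see a contradiction with the Clinical assessment section: "Subjects will be assessed by independent clinicians who will not be involved in the direct clinical care of any of them". That section goes on to describe a semistructured diagnostic interview. The questionnaires stand under a separate heading that promises no independent administrator, and the session-one sentence does not say who gives them. The CID, an interview by name, lends this reading some force, but not enough for a finding.

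**Conclusion.** The point holds, within limits. As written, the treated arms' first questionnaires follow the rationale and, by strong inference, allocation. The waiting-list baseline cannot be taken under matching conditions. Change-based comparisons of either treated arm with the waiting list may therefore be biased.

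The size and direction of that bias cannot be derived from the article. Any arm-specific shift passes in full into a between-arm contrast of change. On the assumptions above, 0.2 SD takes the false-positive rate from 5% to about 11%, but the 0.2 is an illustration, not an estimate.

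The conclusion rests on two inferences: that the session-one questionnaires are the pre-treatment measurement, and that they follow allocation. If the full protocol shows either to be wrong, what remains is a sentence to reconcile. Severity: should be fixed. It does not undermine the VR versus non-VR comparison unless session one shifts those two arms differently.

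**What to change.** Administer all five questionnaires on one occasion that is the same in all three arms, after consent, before the allocation is revealed and before any treatment rationale is given. The clinical assessment that the article already describes is a suitable place. State this timing under Psychometric assessment, and delete the session-one sentence or reconcile it with that timing.

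The cost is a change of wording and moving existing forms to an existing contact. No new instrument or procedure is needed. It has to be done before enrolment, because a baseline already taken after the rationale cannot be retaken.

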**Figure 5 F5:**
[figure not shown]
Form of self-observation of early anxiety signals (adapted from Ost, 1987).

**Figure 6 F6:**
[figure not shown]
Form for registration of homework relaxation training (adapted from Ost, 1987).

### Follow up assessment

Six and twelve-month follow-up are planned in order to verify the efficacy of the treatment over a long term period.

### Potential benefit of VR

The use of VR will be introduced with a goal of increasing the subjects' ability to relax themselves easier than they do using the traditional relaxing methods. If analyses find that the use of VR improves the relaxation processes and the reduction of anxiety, then a range of benefits are possible. For example, satisfactory ability to manage the patient's anxiety could be increased and length of treatment could be reduced.

### Potential harms of VR

Potential for harms is minimal. The only risk really associated with the use of VR is the so-called cybersickness, that is characterized by symptoms that parallel those of classical motion sickness both during and after the virtual experience. Cybersickness is rare and sometimes disappears after few minutes of rest.

### Trial analysis

Data will be entered in SPSS. Descriptive methods will be used to demonstrate the consistency of the three groups, describe participant characteristics and report levels of participation and drop out. Analysis of variance will be used to evaluate baseline characteristics of the three groups involved in the study, overall significance of improvement across outcome measures, and drop out versus maintainers. For each patient, change in psychometric and physiological measures will be calculated and analysed using t-test for matched groups for both intervention and control groups. The magnitude of change will be estimated and the 95% confidence intervals given.

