### Aim of the study

Knowing that relaxation techniques are as effective as cognitive and behavioural methods in the treatment of GAD and considering the critical point regarding the difficult in learning them, the aim of the present study is to investigate the advantages of using a VR-based relaxation protocol in reducing anxiety in patients affected by GAD. The following hypothesis will be tested:

I) GAD patients exposed to a VR relaxing environment learn how to relax themselves easier and more efficiently than patients exposed to a traditional relaxation protocol;

II) There is a positive correlation between the treatment efficacy and the sense of presence experienced by the patients during the treatment sessions.

3-D audio-visual experiences, whose critical aspect is to induce a feeling of presence and engagement, will be presented to the subjects in order to help them to become relaxed. Through the link between the feeling of presence and the emotional state, VR relaxing environments will be used to reduce the anxiety levels in their users [15].

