### Subjects

Patients will be recruited in a public health-care structure in Milan, Italy, according to the diagnosis received from their treating responsible psychiatrist or psychologist. In order to be included in the study, patients have to meet the following criteria: (1) primary diagnosis of GAD; (2) requesting treatment for their GAD; (3) older than 17 and younger than 70; (4) no depressive disorder preceding the current episode of GAD or requiring immediate treatment; (5) no behaviour therapy received for their GAD; (6) no evidence of organic mental disorders accounting for the complaints, mental retardation, psychotic disorders, alcohol or drug dependence; (7) no migraine, headache, seizure disorder, and vestibular abnormalities since they represent significant contraindications for the use of VR.

A power analysis was conducted in order to evaluate the number of patients needed to detect a significant difference (Effect size f ≥ 0,40) between the three groups (VR, non VR and WL) with a power of 0,90. The analysis showed a necessary total sample size of 75, 25 in each group, with α = 0,5, two-tailed. Both males and females will be included. All participants have to be clinically stable, meaning no change in dose of psychotropic medications 1 month before inclusion. Since over 90% of individuals who meet criteria for GAD in a given year will also have at least one other DSM-IV diagnosis [8], patients will be included in the study even if they present at least one more psychiatric diagnosis.

Before participating in the study, each patient will be provided with written information about the study and invited to give written consent for inclusion. The present research is in compliance with the Helsinki Declaration.

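### The planned matched t-tests on change do not test hypothesis I, and no VR versus non-VR contrast or confidence interval is stated

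*Protocol article*

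**What the plan says.** Hypothesis I (Aim of the study) states that patients exposed to VR "learn how to relax themselves easier and more efficiently than patients exposed to a traditional relaxation protocol". This is a comparison between two randomised arms.

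Trial analysis names two inferential methods:

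- **Analysis of variance.** "Analysis of variance will be used to evaluate baseline characteristics of the three groups involved in the study, overall significance of improvement across outcome measures". The same method is to compare drop-outs with those who stay. The text does not say whether improvement is compared between arms, and it names no pairwise contrast.
- **Matched t-tests.** Change in the psychometric and physiological measures "will be calculated and analysed using t-test for matched groups for both intervention and control groups". The next sentence promises an estimate of the size of change with 95% confidence intervals.

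The sample size (Subjects) is set for a three-group difference: "Effect size f ≥ 0,40) between the three groups (VR, non VR and WL) with a power of 0,90". It gives 25 patients per arm.

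**The concern.** A matched t-test on change asks whether an arm improved over time. That improvement mixes the treatment effect with natural course, regression to the mean and attention. The article's own Background describes GAD as chronic and fluctuating, so uncontrolled change is hard to interpret here. The Discussion relies on the non-VR and waiting-list groups to attribute results to the intervention, and only a between-arm estimate can support that.

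Two things are at stake. The stated confidence intervals would describe the wrong quantity for hypothesis I. And if the article's reader sees a significant change in one active arm and not in the other, that contrast is easily taken as a difference between treatments although it has not been tested.

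**Working it through.** **Inputs from the article:** three arms, 25 each; f = 0.40; power 0.90; two-sided test. Alpha is printed as 0.5; I use 0.05 throughout, as presumably meant. **Assumed, because the article gives none:** standardised within-arm changes, differences from waiting list, and pre-post correlations. Each is shown as a range.

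**1. The plan's own figure.** One-way ANOVA, k = 3, noncentrality λ = f²N = 0.16 × 75 = 12, degrees of freedom 2 and 72. Power is 0.869, not 0.90; reaching 0.90 needs 84 patients (28 per arm). So 75 is not reproduced. That and the printed alpha are separate matters on which this point does not depend. What matters here is that the calculation is for an omnibus three-group difference, not for VR against non-VR.

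**2. What the omnibus ANOVA can show.** Let VR = non-VR, both differing from waiting list by D (in SD units). The arm means deviate from the grand mean by D/3, D/3 and −2D/3, so λ = 25 × [2(D/3)² + (2D/3)²] = 25 × 2D²/3.

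- D = 0.8: λ = 10.67, power 0.82.
- D = 1.0: λ = 16.67, power 0.96.

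The test would therefore be significant in 82% or 96% of trials with no VR advantage at all.

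**3. What comparing the matched t-tests can show.** Let both active arms have the same true standardised change dz. With n = 25, the power p of one paired t-test comes from the noncentral t distribution with 24 degrees of freedom and noncentrality dz × √25. The arms are independent, so the probability that exactly one is significant is 2p(1 − p), and that only VR is significant is p(1 − p).

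| dz (assumed) | p | exactly one significant | VR only |
|---|---|---|---|
| 0.3 | 0.302 | 42% | 21% |
| 0.4 | 0.484 | 50% | 25% |
| 0.5 | 0.670 | 44% | 22% |
| 0.6 | 0.821 | 29% | 15% |
| 0.7 | 0.919 | 15% | 7% |
| 0.8 | 0.970 | 6% | 3% |
| 1.0 | 0.998 | 0.5% | 0.2% |

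At large changes the tests fail the other way. If non-VR changes by 0.8 SD and VR by 1.6 SD, both arms are significant in 97% of trials, and the paired tests do not show the difference.

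**4. What a direct comparison would offer.** With 25 per arm, two-sided 0.05 and 80% power, a two-sample t-test detects 0.81 SD of the post-treatment score without adjustment. The variance factor is 2(1 − r) for change scores and 1 − r² for ANCOVA; the detectable difference is 0.81 times the square root of each.

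| r (assumed) | change score | ANCOVA |
|---|---|---|
| 0.5 | 0.81 × √1.00 = 0.81 SD | 0.81 × √0.75 = 0.70 SD |
| 0.6 | 0.81 × √0.80 = 0.72 SD | 0.81 × √0.64 = 0.65 SD |
| 0.7 | 0.81 × √0.60 = 0.63 SD | 0.81 × √0.51 = 0.58 SD |

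The one degree of freedom spent on the covariate is ignored; its effect is negligible here.

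**The case against.** The strongest reply is that a randomised comparison is already planned. The ANOVA of improvement, read together with a sample size built on a difference between three groups, plausibly is a three-group test. That stands: a reader might infer that the trial has no between-arm analysis at all, and the text does not support so strong a claim. But step 2 shows that this test does not isolate VR from non-VR, and the only estimate and interval described follow the matched t-tests.

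Second, the article gives the paired tests no decision rule. A reader might infer that the plan will declare superiority when VR is significant and non-VR is not; the text never says so. The figures in step 3 are therefore conditional on someone making that comparison. They also depend strongly on the assumed change: they nearly vanish at 1.0 SD, which is not implausible for a training the article regards as effective.

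Third, contrasts after an ANOVA are often left to an analysis plan, which is not at hand. That would answer a complaint about missing detail. Here, however, the article does state how change is analysed, and that analysis does not match its hypothesis.

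Fourth, ANCOVA is not the only valid choice. Under randomisation, a between-arm comparison of unadjusted change scores is also valid; ANCOVA is more precise. The gain should be measured against change scores, which the plan uses, and not against unadjusted post-treatment scores.

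A different reading of the matched test, pairing patients across arms, does not help: the arms are randomised independently and no matching is described.

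**Conclusion.** The point holds in a limited form. As written, the change analysis and its confidence intervals are within-arm quantities and do not test hypothesis I. The ANOVA may compare the three arms, but it can be significant because of the waiting list alone (82% of trials at an assumed 0.8 SD), and no VR versus non-VR contrast or interval is stated. If the arm-by-arm results were compared, equal true change would produce a discordant pair in 42% to 50% of trials for assumed changes of 0.3 to 0.5, falling to 0.5% at 1.0, with VR the only significant arm in half of these. The structural mismatch does not depend on any assumption; the percentages do. The ANOVA tests of baseline balance and the definition of the analysis set are not part of this point.

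**What to change.** In Trial analysis, state that hypothesis I is tested by the VR minus non-VR difference in post-treatment score, from an ANCOVA with arm as factor and the baseline score as covariate, reported with its 95% confidence interval. Report each active arm minus waiting list as supporting contrasts. Keep the matched t-tests and within-arm changes as description only.

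If the investigators prefer change scores, an unadjusted between-arm comparison of change would also answer the hypothesis, at some loss of precision: a detectable difference of 0.72 instead of 0.65 SD at an assumed correlation of 0.6.

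The cost is a few sentences of analysis text. The questionnaires are already scheduled before and after treatment, and SPSS, the software named, fits the model. No change to design, visits or sample is needed for this point.
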